### Randomization & implementation

Matched-pair blocks were created on the basis of the county characteristics of: percentage of opiate admissions; population covered; and ratio of opiate addiction treatment admissions to physicians licensed to prescribe buprenorphine [26]. The cut-off criteria used for matching, based on the median measures from the 2011 Ohio Department of Alcohol and Drug Addiction Services treatment organization dataset, were: 20% opiate admissions (above/below); 200,00 people covered (above/below); and 50 treatment admissions per physicians in the county registered to prescribe buprenorphine per annum (above/below). As a result, seven county board matched-pairs were identified. A random number generator was utilized within the seven county board pairs to assign organizations into one of the two study conditions. Study staff completed enrollment and received consent approval from the county boards as well as providers. No visible concealment was applied, and blinding of participants and researchers was considered infeasible due to logistical reasons.

### Data analysis

Because the number of treatment organizations within an ADAMHS Board is small (n = 2 to 8) we intend to use an optimal design in which treatment arms are allocated following a multi-site cluster randomization procedure [27,28]. The initial exploratory analyses of both outcomes and covariates will assess standard summary statistics and graphical presentations. Scatter plots and correlation analyses identify possible associations between outcome and predictor variables. The analysis will represent the multi-site cluster randomized trial as a mixed-effects model; percentage of buprenorphine use by opioid dependent patients is nested within cluster (treatment organization); and clusters are nested within site (ADAMHS board). In this mixed-effects model, there will be random effects due to county board and organization; fixed effect due to study arm and time. For the percent of opioid admissions receiving buprenorphine, a logistic regression analysis will be performed. We will examine the Advancing Recovery effect using a separate model at each time point and in an omnibus growth curve model that includes the main effects of Advancing Recovery and Time as well as the interaction between Advancing Recovery and Time. The percent of opioid patients receiving buprenorphine will be measured monthly for each organization, and it is expected that these values will be correlated over time. Therefore, instead of assuming an independence (*i.e*., zero correlation) or a compound symmetry covariance structure (*i.e*., a constant correlation regardless of the proximity of measurement time points), we will allow errors to be first-order auto-correlated, denoted as AR (1). This can be done by allowing an additional parameter in the mixed-effects model that represents the correlation between the two most adjacent measures of Opioid Patients Receiving Buprenorphine. This correlation is reduced exponentially as the measures become further apart.

For the ADAMHS board and organizational covariates, at each time point we will assess moderation by including each potential moderator as an independent variable and as an interaction with the Advancing Recovery effect. Statistical significance of the interaction effect will indicate the presence of moderation. The estimate for the effect size of moderation, which is cross-level interaction, is between 0.17 and 0.19.

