**Methods:**

The Advancing Recovery Buprenorphine Implementation Study is a cluster-randomized controlled trial designed to increase use of the evidence-based practice buprenorphine medication to treat opiate addiction. Ohio Alcohol, Drug Addiction, and Mental Health Services Boards (ADAMHS), who are payers, and their addiction treatment organizations were recruited for a trial to assess the effects of payer and treatment organization changes (using the Advancing Recovery Framework) versus treatment organization changes alone on the use of buprenorphine. A matched-pair randomization, based on county characteristics, was applied, resulting in seven county ADAMHS boards and twenty-five treatment organizations in each arm. Opioid dependent patients are nested within cluster (treatment organization), and treatment organization clusters are nested within ADAMHS county board. The primary outcome is the percentage of individuals with an opioid dependence diagnosis who use buprenorphine during the 24-month intervention period and the 12-month sustainability period. The trial is currently in the baseline data collection stage.

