## Methods

### Trial design

The participating ADAMHS boards have been randomized into two study conditions. In the Control Arm (Arm 1), participants will use the NIATx model for organizational change only. In Arm 2, participants will use the Advancing Recovery Framework that includes the payer intervention and NIATx models. Payers will not play a direct role in the control arm. The NIATx organizational change model (Figure 1) was chosen as the control condition because research exists that suggests organizational change models alone may be sufficient for EBP implementation [19,20]. A cluster randomized controlled design was used to study the effects that payers (or county ADAMHS boards) and treatment organizations have on buprenorphine adoption and also to control for ‘contamination’ across the treatment and control arms. A 1:1 allocation ratio of counties was utilized in the randomization.

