### Participants

Ohio Alcohol, Drug Addiction and Mental Health Boards (ADAMHS) coordinate the public behavioral health system in Ohio. Each board covers one to five of Ohio’s 88 total counties and disperses Substance Abuse and Prevention Treatment (SAPT) block grant funds, as well as funds from local levies directed to addiction services. These Boards are responsible for 55% of addiction treatment services funding and often have responsibility for the quality and cost effectiveness of addiction treatment services within their jurisdictions [21]. The boards contract with provider organizations to deliver addiction and mental health treatment services. All 46 of Ohio’s ADAMHS boards were eligible for the study. The ADAMHS boards were recruited through an invitation from the Ohio Association of County Behavioral Health Authorities from May to September, 2012. The study team also actively recruited ADAMHS boards needed to meet the study’s matching criteria. A total of 14 boards representing 23 counties agreed to participate (Figure 2). Within each board jurisdiction, treatment agencies with 75 or more annual admission were invited to participate in the study. Fifty treatment agencies volunteered. Two to eight treatment agencies are participating per board.

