### Sample size

To determine sample size, we fit a linear mixed-effects model to the monthly results for the performance measure of percent opioid dependent patients receiving buprenorphine from each of the participating organizations and estimate the ‘payer-treatment organization’ effect. A mixed-effect model was selected instead of conventional regression models because, first, the mean outcomes for a given treatment organization are expected to be correlated from month to month. A mixed-effect model allows for auto-correlated error terms. Second, a number of unobservable treatment organization characteristics are likely to influence the key measures. Random effects at the treatment organization level can be employed within the mixed-effect model to capture the correlation introduced by such characteristics. Proper reflection of auto-correlation and random effects allows for more reliable estimates of the fixed effects, starting in months 6 to 11 (for baseline), then during months 12 to 36 (intervention stage), and through months 37 to 50 (follow-up stage). The power of the study design is determined by the anticipated standardized effect size based on effects experienced in the Advancing Recovery pilot project. The Advancing Recovery pilot data found that the payer-treatment organization intervention increased buprenorphine use rates from 6% to 43%, with an estimated standard deviation of 23.5% based on a sample size of 1,016. This yields an effect size of 0.935. Intraclass correlation (ICC) among counties affects the power of cluster-randomized trials [24]. An estimate of ICC is around 0.05. For this study, a dropout rate of 20% is being proposed, giving a total of 40 organizations available for analysis. With a total of 40 treatment organizations, each with an average of 91 patients, the study will achieve at least a power of 0.82 with a one-tailed type I error rate of 0.05. Power and sample size calculations were performed using Optimal Design Software by Raudenbush (Version 3.01) [25]*.*

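### As described, the growth curve model leaves between-board variation in trend out of the arm-by-time test, so its standard error is too small if boards differ in trend

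*Protocol article*

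**What the plan says.** All model statements are in the Data analysis section of the protocol article.

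- **Random and fixed parts:** "there will be random effects due to county board and organization; fixed effect due to study arm and time". Time appears only in the fixed part. Neither intercepts nor slopes are named.
- **Growth model:** the effect is examined by separate models per time point. A further analysis is described as: "omnibus growth curve model that includes the main effects of Advancing Recovery and Time as well as the interaction between Advancing Recovery and Time".
- **Correlation over time:** the article rejects independence and compound symmetry and adopts AR(1) errors for the monthly organization values, described as one additional parameter.

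On the design, the abstract reports a matched-pair randomization "resulting in seven county ADAMHS boards and twenty-five treatment organizations in each arm", and Trial design says "A 1:1 allocation ratio of counties was utilized in the randomization". Under Participants, "Two to eight treatment agencies are participating per board". The Sample size section places baseline in months 6 to 11, intervention in months 12 to 36 and follow-up in months 37 to 50.

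**The concern.** The arm-by-time interaction is a difference between two average trends, each averaged over seven randomized boards. Its sampling error therefore has to include how much trends differ between boards within an arm. A random intercept shifts a board's or organization's level and cancels from its slope. An AR(1) process can absorb some drift within a single organization, especially when the correlation is high, but it is independent from one organization to the next. It cannot represent a rise or fall common to all organizations under one payer.

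Without a slope variance at board level, the interaction is judged mainly against monthly noise over 50 organizations. Ordinary differences in trend between boards could then be read as an effect of the payer intervention. This trial gives reason to expect such differences. The Discussion calls each board a distinct payer environment, and Table 1 has each Arm 2 board find its own barriers and develop its own tactics.

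**Working it through.** **Plan's own figure.** There is none for this test. The article's power of 0.82 reproduces as a two-sided two-sample t test on 20 + 20 independent organizations with effect size 0.935 (0.822; one-sided 0.896). That calculation involves no trend, so it supplies no slope variance.

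**Inputs from the article.** 14 boards, 7 per arm; 25 organizations per arm, 2 to 8 per board; SD 23.5 points; ICC 0.05; months 12 to 36 (25 monthly values) or months 6 to 50 (45 values); one-tailed 0.05 (Sample size).

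**Assumptions, not in the article.**
- Time is linear on the percentage scale, with slope expressed as change over the analysed period.
- Organizations per board are 2, 2, 3, 3, 3, 4, 8 in each arm (sum 25).
- The total variance 23.5² is split into board, organization and residual shares of 0.05/0.55/0.40 or 0.05/0.15/0.80.
- Monthly correlation ρ is 0.3 to 0.9.
- Board slope SD is 5 or 10 points over the period, with organization slope SD either zero or equal to it.

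**Formula.** With random intercepts only, every organization gets about equal weight in the slope contrast, so

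true SE² = SE₀² + 2·σ_b²·Σn_b²/(Σn_b)² + 2·σ_o²/25,

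where SE₀ is the standard error with no slope variation, σ_b and σ_o are the board and organization slope SDs, and n_b is the number of organizations in a board. Real one-sided error = P(Z > 1.645 × model SE / true SE). For two-sided error, double the tail and use 1.96.

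**One case in full** (25 months, ρ = 0.6, first split, σ_b = 10, σ_o = 0):
- Σn_b² = 4 + 4 + 9 + 9 + 9 + 16 + 64 = 115, and 115/625 = 0.184.
- The board term is 2 × 100 × 0.184 = 36.8.
- SE₀ = 4.73, so true SE = √(22.37 + 36.8) = 7.69.
- The model's own SE, once its variance parameters have settled on the best-fitting wrong values (fitted ρ rises to 0.62), is 4.98.
- 1.645 × 4.98/7.69 = 1.065, giving 14.3% one-sided. 1.96 × 4.98/7.69 = 1.269, giving 20.5% two-sided.

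**Range over both splits, 25 and 45 months, ρ 0.3 to 0.9:**

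| Board slope SD over period | One-sided, nominal 5% | Two-sided, nominal 5% |
|---|---|---|
| 0 (no organization slopes either) | 5% | 5% |
| 5 points | 6.0–13.9% | 6.4–19.6% |
| 10 points | 8.6–24.1% | 10.4–40.3% |

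The low ends occur at ρ = 0.9 and the high ends at ρ = 0.3 with 45 months. If slopes differ only between organizations (SD 10), the two-sided error is 5.4–14.6%, so the board-level omission matters most.

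**Simulation check** (REML, 300 runs per setting, 25 months, ρ = 0.6). The Monte Carlo standard error at 13.7% is √(0.137 × 0.863/300) = 2.0 points.

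| Slope SD, board/organization | Fitted model | Mean SE | Actual SD | One-sided (z) | Two-sided (z) |
|---|---|---|---|---|---|
| 0/0 | as described | 4.7 | 5.0 | 5.7% | 6.7% |
| 5/5 | as described | 4.8 | 5.8 | 8.7% | 11.3% |
| 10/10 | as described | 5.2 | 8.1 | 13.7% | 20.3% |
| 10/10 | with both random slopes | 7.8 | 7.8 | 5.3% | 6.7% |

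Referring the third row to t with 12 df still gives 10.3% one-sided, so changing the degrees of freedom alone does not repair it. The fourth row on t with 12 df gives 5.0% both one-sided and two-sided.

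**The case against.** The best defence is that the article never says intercepts only. Growth curve models often carry random slopes, a fixed effect of time does not exclude one, and a condensed article may leave the full structure to a document not shown. This stands as a limit: a reader may not conclude that random slopes have been ruled out. But the article does commit itself to a structure. It assigns time to the fixed part, names two random effects, and argues for AR(1) as its answer to correlation over time. An analyst following that text would fit intercepts.

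Other points stand in part.
- The article does not name the interaction as the decisive test, and the primary outcome is a percentage during the intervention and sustainability periods, not a slope. The separate time-point models contain no time trend and are untouched.
- It mentions logistic regression for this percentage and does not say that time is one linear term. The mechanism carries over to those forms, but the percentages above do not.
- The 7% to 58% spread of use in the Discussion concerns levels, not trends, so it cannot be used to set the slope SD.
- Only a one-tailed 0.05 is stated, so the larger two-sided figures should not lead.

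A reader might infer that false positives will multiply whatever the data look like, or that the whole intervention analysis is invalid. The documents support neither. The inflation depends on an unstated variance and is slight at the mild end (6.0% one-sided).

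**Conclusion.** The point holds conditionally. On its natural reading, the described model tests the Advancing Recovery-by-Time interaction without the between-board slope variance that randomizing 14 boards calls for. If boards differ in trend, the standard error is too small. Under the assumed board slope SDs of 5 to 10 points over the period and ρ of 0.3 to 0.9, the true error at a nominal one-sided 5% is about 6% to 24%. It is mild when ρ is high or the slope SD is small, and close to nominal with no slope variation. The direction follows from the design. The size rests on assumed slope variances, a linear trend on the percentage scale and an assumed spread of organizations over boards.

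**What to change.** State in the Data analysis section that the growth curve model includes a random slope for time at board level, and one at organization level where it can be estimated. Test the interaction on board-level degrees of freedom: about 14 − 2 = 12, fewer if the pairs are modelled (7 − 1 = 6 for a comparison within pairs). State in advance that, if the model does not converge, board-specific slopes or changes will be compared between arms within the matched pairs. This fallback matters, because slope variances are hard to estimate with 14 boards of 2 to 8 organizations. Piecewise time is optional and does not address this point.

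The change needs no new data, and the article reports that baseline collection has only begun. The cost is wider confidence intervals and some loss of nominal power for the interaction. In the simulated case the reported standard error rises from 5.2 to 7.8, while the estimate's actual spread is about the same (8.1 against 7.8). The wider interval there reports uncertainty that was already present.

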### Objectives

The primary research question is to determine if the Advancing Recovery Framework increases the use of buprenorphine in addiction treatment organizations. The secondary research question is to determine if county characteristics (*e.g*., percentage of opioid abusers, existing addiction treatment medication availability, and payment policy) and organizational characteristics (*e.g.*, organization size, access to physicians, number of nurses, percentage of clinicians with graduate degrees, and patient demographic characteristics) can moderate the delivery of buprenorphine.

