The five levers described in the planning phase provide a mechanism for payers to identify systemic barriers to EBP use and promote change. The ‘customer impact analysis’ examines how the EBP benefits the customer, affects the number or type (*i.e.*, demographic) of customers involved in treatment, and which customers are needed to advocate for the change. A ‘financing and purchasing analysis’ determines how financing, reimbursement and payment provide incentives for EBP use. The ‘regulatory and policy analysis’ uncovers regulatory barriers. The ‘operations analysis’ assesses the training and skill-building payers and treatment organizations need for EBP implementation. Finally, an ‘inter-organizational analysis’ identifies what other organizations need to be involved to remove regulatory or financing barriers.

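### Calling any significant interaction moderation, across eight or more moderators at each time point, makes a false moderator likely

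*Protocol article*

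**What the plan says.** Moderation is the secondary research question (Objectives: "The secondary research question is to determine if county characteristics" and organizational characteristics moderate delivery of buprenorphine). Two lists of examples follow. The county list is "percentage of opioid abusers, existing addiction treatment medication availability, and payment policy". The organization list is "organization size, access to physicians, number of nurses, percentage of clinicians with graduate degrees, and patient demographic characteristics". That makes three plus five, and both lists are introduced as examples.

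The Data analysis section fixes the method and the decision rule:

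- Method: "at each time point we will assess moderation by including each potential moderator as an independent variable and as an interaction" with the intervention effect.
- Decision: "Statistical significance of the interaction effect will indicate the presence of moderation".
- Size: "The estimate for the effect size of moderation, which is cross-level interaction, is between 0.17 and 0.19".
- Outcome frequency: "The percent of opioid patients receiving buprenorphine will be measured monthly for each organization".

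For the main effect, the same section pairs the separate time-point models with an omnibus growth curve model. For moderation it gives only the time-point analysis.

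**The concern.** The rule is a positive criterion for declaring a finding. It is applied to many moderators and, as written, repeated over time. A single nominally significant interaction at any time point meets it. The article expects monthly values within an organization to be correlated, so a chance interaction would tend to persist into neighbouring months and could look like replication.

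At stake is the answer to the secondary question: which counties and organizations benefit more from involving the payer. A list of moderators produced this way would probably contain at least one spurious entry, with nothing in the rule to show which.

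Two related matters are left open. Payment policy is a listed moderator, and one of the five payer levers applied in Arm 2 "determines how financing, reimbursement and payment provide incentives for EBP use". The time at which this moderator is measured therefore matters, and the article does not state it. The effect size of 0.17 to 0.19 comes without scale, alpha or power, so it does not tell the reader what the moderation analysis can detect.

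**Working it through.** **Inputs from the protocol article**

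- Named moderators: 3 county + 5 organization = 8 (Objectives).
- Time points: months 12 to 36 are 25 and months 37 to 50 are 14, so up to 39 after baseline (Timeline, Sample size). The Abstract's 24 + 12 months would give 36.
- 40 organizations, 91 patients each, ICC 0.05, one-tailed 0.05 for the main effect (Sample size).
- 14 boards (Participants).

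**Assumptions:** alpha 0.05 per interaction test, independent moderators, no true moderation.

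**Step 1. One time point.** P(at least one false moderator) = 1 − 0.95^8 = 0.34.

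**Step 2. Expected false positives if every month is tested.** 8 × 39 = 312 tests and 312 × 0.05 = 15.6. With 36 months, 8 × 36 = 288 and 288 × 0.05 = 14.4. Correlation between months does not change these expectations.

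**Step 3. Chance of at least one over 39 months.** This does depend on correlation. I simulated eight independent series of z-statistics with first-order autocorrelation, tested two-sided at 0.05.

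| Month-to-month correlation of test statistics | P(at least one false moderator) | Mean number of the 8 falsely flagged |
|---|---|---|
| 0.5 | 1.00 | 6.5 |
| 0.9 | 0.995 | 3.9 |
| 0.95 | 0.97 | 2.7 |
| 0.99 | 0.74 | 1.2 |

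If the correlation is instead the same between all pairs of months, at 0.95, the chance is 0.68. If only one time point is used, it is the 0.34 of Step 1.

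**Step 4. What could 0.17 to 0.19 mean?** The article gives no power for moderation, so there is no stated figure to reproduce. I therefore tried readings of the effect size. With organizations treated as independent units, the standard error of the arm effect is √[4(ICC + (1 − ICC)/m)/J] = √[4(0.05 + 0.95/91)/40] = 0.0777. One-tailed power at 0.05 for 0.17 and 0.19 is:

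| Reading of the moderator | Power |
|---|---|
| Organization-level, continuous, per SD (SE 0.0777) | 0.69–0.77 |
| Organization-level, binary, split 50/50 (SE 0.155) | 0.28–0.33 |
| Patient-level, binary | 0.84–0.90 |
| Board-level, continuous, per SD, 14 boards | 0.36–0.42 |
| Board-level, binary, 14 boards | 0.16–0.18 |

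The smallest per-SD effect detectable with 80% power, one-tailed, is (1.645 + 0.842) × 0.0777 = 0.193 with 40 organizations. With 50 it is 0.173. The stated range may therefore itself be a minimum detectable effect, but the article does not say so.

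**The case against.** The strongest reply is that this is a condensed article. Multiplicity control, degrees of freedom and covariate timing often sit in an analysis plan that is not shown, and moderation is only the secondary question. That stands as far as omissions go. It does not cover the decision rule, which is printed: a corrected analysis plan would have to override that sentence, not add to it.

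A second reply is that the article does not fix which time points are used for moderation, and that persistent test statistics reduce the number of independent chances of error. This also stands. It is why the result is given as a range, with 0.34 for a single time point. Positive correlation among the moderators would also lower these probabilities.

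Three stronger readings are tempting and are not supported:

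- **That false positives are guaranteed.** They are likely, but the probability falls to about 0.7 under very high persistence and to 0.34 with one time point.
- **That power for 0.17 to 0.19 is at best about 0.3.** That figure needs a balanced binary organization-level moderator. Several named characteristics, such as organization size and number of nurses, are naturally continuous, and Step 4 gives 0.69–0.77 for that case. Power is clearly low only for county characteristics with 14 boards. Power within a single month would need monthly patient counts, which the article does not give.
- **That mediators are being mislabelled as moderators.** The phrase about each time point says when moderation is assessed, not that covariates are re-measured then. The word existing in the county list points to pre-intervention status. A baseline value of payment policy is a legitimate moderator even if the intervention later changes policy. What can fairly be asked is that the timing be stated.

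**Conclusion.** The concern holds for the decision rule. As written, the plan declares moderation from any significant interaction, over at least eight example moderators and repeated time points of a monthly outcome. With alpha 0.05, independent moderators and no true moderation, the chance of at least one false moderator is 0.34 at one time point. Over all 39 monthly points it is about 0.74 to 1.00 for first-order correlations of the test statistics from 0.99 to 0.5, with about 16 false positives expected. A wrong answer to the secondary question is therefore probable, though not certain. The primary conclusion is unaffected.

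The range 0.17 to 0.19 cannot be judged adequate or inadequate until its scale, alpha and power are given. The moderator timing needs clarifying; it is not a demonstrated error. The change should be made before outcome data are analysed. The trial is still in baseline collection, so there is time.

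**What to change.** Replace the per-time-point rule in the Data analysis section as follows:

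1. Test one arm-by-moderator interaction per moderator on the intervention-period contrast, with the sustainability period as supportive.
2. State that every moderator takes its pre-intervention value (baseline months 6 to 11 or earlier), because payment is a lever of the Arm 2 intervention.
3. For county characteristics, use board-level degrees of freedom, based on 14 boards.
4. List the moderators and control the set by Holm or false discovery rate. Alternatively, report interaction estimates with confidence intervals as exploratory and delete the sentence that equates significance with moderation.
5. State the scale, alpha, sidedness and power to which 0.17 to 0.19 refers, separately for organization and county moderators.

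This changes analysis wording only. The price is fewer nominally significant moderators and no claims of moderation in particular months.
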